## Background

Globally, of the 50 most prevalent chronic diseases, four are related to oral health: (1) dental caries of permanent teeth, (2) chronic periodontitis, (3) dental caries of deciduous teeth and (4) edentulousness (total tooth loss) [1, 2]. Tooth loss is predominantly a consequence of dental caries in the permanent dentition and adult chronic periodontitis, and potentially results in substantial social and health consequences. Dental caries in the deciduous dentition is a significant predictor of dental caries in the permanent dentition [3]. With few exceptions, both dental caries and periodontitis are preventable conditions with adequate self-care and healthy lifestyle habits, with additional health promotion and preventive interventions at the health services level [4, 5]. However we continue to struggle to significantly reduce, and preferably eradicate, the burden of preventable oral health conditions. Appropriate self-care is largely dependent on the social and health capital of the community [6]. In disadvantaged, marginalised, rural and Indigenous communities, this is often absent. These communities also have the additional burden of limited health promotion and preventive services, carry a significant health burden and suffer a seriously reduced oral health-related, and overall quality of life [7, 8].

Most dental health promotion and preventive services require professionally trained personnel, needing equipment and regular availability of the service for the re-application of interventions. The current evidence is that a number of dental preventive interventions require re-application 2 to 4 times a year [9, 10]; and in disadvantaged and especially remote communities, this is usually not possible, and the burden of the common oral diseases is never dealt with: more importantly, never prevented. To our knowledge there is currently no evidence on the effectiveness, cost-effectiveness and cost-benefit of a less frequent and therefore sustainable dental preventive intervention strategy.

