An oral health survey in 2004 (pre-water fluoridation) in the Northern Peninsula Area (NPA) of far north QLD, found that dental caries experience of 6- and 12-year-old children was more than twice that of the state average and more than four times greater than the comparable figures for Australian children overall. Soon after this survey the reticulated water supply of the five small rural communities in this area was fluoridated. A follow-up oral health survey in NPA conducted in November 2012 by this team, in which we examined over 70 % of known resident schoolchildren (*n* = 339), suggests that the dental caries status has improved significantly since the 2004 survey [18]. Few teeth had restorations in both surveys. Age-weighted overall caries prevalence and severity declined from 2004 to 2012 by 37.3 %. The effect was most marked in younger children, dmft decreasing by approximately 50 % for ages 4 to 9 years; at age six, mean decayed score decreased from 5.20 to 3.43. DMFT levels decreased by half in 6 to 9 year old children. However, significant unmet treatment needs exist at all ages. To address this, practical and affordable ways have to be found.

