## Methods

### Study design

This is a longitudinal preventive intervention study. All school children in the NPA will be invited to participate. As it is unethical to withhold any proven intervention from any child, no control group will be created. Children who do not consent to participate may be natural controls if they consent to a dental examination at the end of the study. The actual caries increment in the children who participate will be compared to the expected caries increment modelled on oral health surveys carried out in this community in 2004 (pre-water fluoridation); in 2012 (by the Griffith University team post-partial water fluoridation) and 2015 (baseline survey for this study).

All consenting children will undergo a detailed head, neck and dental clinical examination and complete a questionnaire on their basic demography (gender and age), residential history (exposure to fluoridated drinking water), own general and oral health perceptions; oral health behaviours, attitudes and knowledge; dental visits; diet and oral health-related quality of life.

All active disease will be treated prior to implementing the dental caries preventive intervention. In years 2 and 3 of the study, all participating children will be invited to return for a dental examination, treatment of new incident disease and repeat of the prevention regime.

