### Intervention

The proposed “Big Bang” preventive intervention is to firstly reduce the pathogenic bacterial load, then seal grooves on posterior (molar) teeth, and thirdly to strengthen the tooth structure.

Oral health promotion will essentially educate children regarding appropriate health behaviours to maintain oral health, with emphasis on the importance of toothbrushing with fluoridated toothpaste, healthy eating habits, emphasising the role of sugar in the tooth decay process, and the importance of reducing both the quantity and frequency of sugary products in the diet.

Prior to the annual intervention the research team will undertake clinical examination of all consenting school-age children to assess dental caries experience. A team comprising of a dentist and/or oral health therapist will treat all existing tooth decay and other oral health problems. Each child will receive the preventive intervention when other treatments are completed.

Prior to the treatment of existing disease, we will investigate saliva of the participants as a component of caries risk assessment. Saliva will be collected using commercially available test kits for measurement of flow rate, pH, buffering capacity and then cultured for bacterial assessment [33]. The number of teeth, fillings and other retentive sites in mouth influence the bacterial load and a high count of bacteria in dental plaque correlates with salivary bacterial counts, making it possible to assess saliva for cariogenic microbes [34, 35]. Such kits use selective media for mutans streptococci and for lactobacilli.

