### Primary outcome variable

The International Caries Detection and Assessment system (ICDAS-II) for clinical caries diagnosis will be used to record caries experience and to determine incidence [36]. This will be measured annually across the 3 years of the study, at baseline and after years 2 and 3 of the project.

ICDAS-II consolidates features of several caries classification systems into one universal system using a six-point ordinal scale ranging from non-cavitated to extensive cavitated lesions to describe any signs of past or present caries activity. Unlike World Health Organisation (WHO) caries detection criteria, ICDAS-II allows the detection of initial/non-cavitated carious lesions, and is thus considerably more sensitive, whilst allowing the extraction of data comparable to previous surveys which used WHO criteria [37].

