### Covariates

The relationship between the primary and secondary outcomes and the preventive intervention will be adjusted for known risk factors for dental caries - oral hygiene behaviours and diet (sugar consumption).

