### Analysis

All baseline socio-demographic characteristics will be described for the selected sample using counts and frequencies. Baseline and follow-up caries experience and questionnaire related information will be reported. Dental caries increment (incidence) will be the main outcome measure used to determine the effectiveness of the preventive intervention. The expected caries increment will be modelled from the three oral health surveys conducted in this community (2004; 2012 and 2015) and compared with the actual caries increment from 2015–2016; 2016–2017 and 2015–2017. The mean caries increment will be compared between the expected (modelled) and actual findings, and adjusted for known risk factors for dental caries. The hypothesis will be that caries increment observed in the period of 2015 to 2017 is smaller than the modelled caries increments. Two independent samples *t*-test will be used for the analysis with significance being determined if *p* < 0.05.

Children who receive only a part of the intervention will be separately assessed: for example we will have children who fully participate, those with baseline and only a year 1 follow-up, those with baseline and only a year 2 follow-up. This will ‘naturally’ further inform us on the most appropriate frequency of this preventive strategy. Both a group and matched analysis will be conducted to account for children who receive only part of the intervention.

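### The stated adjustment set leaves out age and baseline caries, and the named two-sample t-test cannot carry any covariate

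*Protocol article*

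**What the plan says.** The Covariates section of the protocol article is one sentence. The relation between outcomes and intervention will be "adjusted for known risk factors for dental caries - oral hygiene behaviours and diet (sugar consumption"). The list follows a dash and names two items. The Analysis section says that the mean increment will be "compared between the expected (modelled) and actual findings, and adjusted for known risk factors for dental caries". It adds no further variable and names an independent two-sample t-test at p < 0.05.

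Other sections bear on what could have been listed:

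- Background: "Dental caries in the deciduous dentition is a significant predictor of dental caries in the permanent dentition".
- Background, on the burden of caries in Indigenous communities, comparing 2004 with 2012: "at age six, mean decayed score decreased from 5.20 to 3.43". The earlier surveys therefore report caries level by age.
- Study design: children "complete a questionnaire on their basic demography (gender and age").
- Primary outcome variable, on ICDAS-II caries: "This will be measured annually across the 3 years of the study, at baseline and after years 2 and 3 of the project". The same section says that data comparable with the earlier WHO-criteria surveys can be extracted.
- Study participants: ages run from 4 to 17 years.
- Study design and Analysis: there is no control group, and the expected increment is modelled from the 2004, 2012 and 2015 surveys.

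**The concern.** In an uncontrolled comparison, only the model for the expected value and the covariates can make the two sides alike in prognosis. Ages 4 to 17 span deciduous, mixed and permanent dentition, so the number of teeth at risk and the likely increment vary with age. Starting caries is the one predictor of later caries that the article itself singles out. Neither is in the adjustment set.

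The two behaviours that are listed come from this study's questionnaire, and nothing in the article shows that the 2004 or 2012 surveys recorded them. The article therefore does not show that the stated adjustment can be made on the expected side.

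There is also a conflict inside the Analysis section. It promises an adjusted comparison but names a test that compares two raw means. As written, not even the two listed covariates can enter the primary test.

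At stake are bias, if the participants' age mix or starting caries differs from that behind the expected value, and some precision.

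**Working it through.** **No figure to reproduce.** The article gives no standard deviation, effect size, power calculation or correlation between baseline caries and increment. The sizes below rest on assumptions, shown as ranges.

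**What is available on each side**

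| Variable | Participants | 2004 and 2012 surveys |
|---|---|---|
| Age | collected | caries reported by age |
| Caries level | ICDAS-II at 2015 baseline | reported, by age |
| A child's starting caries paired with a later increment | 2015 to 2017, under intervention | not described |
| Oral hygiene, sugar | questionnaire | not described |

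Age is firmly shared. Caries level is shared at group level. A per-child baseline paired with an increment without the intervention is not shown to exist.

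**Precision.** If baseline caries correlates with the increment at rho, adjustment multiplies the residual variance by 1 − rho² and the standard error by √(1 − rho²). The gain in effective sample size is 1/(1 − rho²) − 1.

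| rho (assumed) | Variance factor | SE factor | Effective sample gain |
|---|---|---|---|
| 0.2 | 0.96 | 0.98 | 4% |
| 0.3 | 0.91 | 0.95 | 10% |
| 0.5 | 0.75 | 0.87 | 33% |
| 0.6 | 0.64 | 0.80 | 56% |

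To put this on a scale, take 339 children (the 2012 survey) against 600 (the lower end of those invited) as illustrative group sizes. The smallest difference detectable with 80% power at two-sided 0.05 is (1.96 + 0.84) × √(1 − rho²) × √(1/339 + 1/600). This is 0.190 SD with no adjustment, 0.182 SD at rho = 0.3 and 0.152 SD at rho = 0.6. Power for a difference of 0.2 SD goes from 83.7% to 87.0% and 95.7%. The calculation treats the expected side as a sample of children with adjustment possible on both sides, which the article does not establish.

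**Bias.** Bias = slope × gap in starting caries. The article gives no gap between participants and the modelled children. The only documented difference between source surveys is at age six: 5.20 − 3.43 = 1.77 decayed teeth. Used as an illustrative gap, with assumed slopes in new lesions per baseline decayed tooth:

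- slope 0.05: 0.05 × 1.77 = 0.09 lesions
- slope 0.10: 0.10 × 1.77 = 0.18 lesions
- slope 0.20: 0.20 × 1.77 = 0.35 lesions

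If the expected increment is predicted for the same children at their own age and starting caries, the gap is zero and so is bias from this source. The sign of any gap is also unknown. A gap in one direction would mimic benefit, and in the other would hide it.

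**The case against.** The strongest reply is that the alignment may already sit in the model. One of its three sources is the 2015 survey, which is the participants' own baseline. The Markov section contrasts intervention data with a non-intervention scenario modelled from baseline and follows children by year of age from 6 to 17. The Background reports an age-weighted change between surveys. A condensed article may fairly leave the model's detail to a fuller document. This stands as far as it goes: it makes the bias conditional. It does not cover the covariate list, which the article fixes, or the t-test, which it names.

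A reader might infer that every survey holds each child's baseline caries, so that adding one covariate settles the matter. The documents do not support that. The 2004 and 2012 surveys are described as separate surveys, with no follow-up or linkage of individual children.

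A reader might also infer that the primary test is shown to be invalid. Assuming a baseline gap of 0.2 to 0.3 SD, correlations of 0.3 to 0.5 and 300 children per side, the bias is 0.06 to 0.15 SD against a standard error of √(2/300) = 0.082 SD, and a nominal 5% test would reject in 11% to 45% of null trials. The arithmetic is right, but none of those inputs is in the article, the range leaves out a zero gap, and it counts rejections in either direction.

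Finally, the article names deciduous caries as a predictor of permanent caries. It does not name age, nor does it call caries the strongest predictor. The case for age rests on the 4–17 range and the age-specific survey results.

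**Conclusion.** The point holds in a limited form. Two things are certain from the text: the stated adjustment set omits age and baseline caries, and the named t-test cannot deliver the adjustment that the same section promises. Whether the estimate is biased cannot be settled from the article, because it does not say how age and caries level enter the expected-increment model. Bias ranges from zero upward, to about 0.35 lesions under the illustrative gap and slopes above, with unknown sign. The precision cost is about 2% to 20% in standard error for assumed correlations of 0.2 to 0.6, which is small at the lower end. This should be corrected, but it does not show that the study's conclusion would be wrong.

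**What to change.** 1. In Covariates, make age, sex and 2015 baseline caries experience (by dentition) the primary set. Keep baseline oral hygiene and sugar as a secondary adjustment, since nothing shows that the earlier surveys recorded them.
2. In Analysis, state that the expected increment is computed for the participating children's own age and sex distribution. Condition it on baseline caries as far as the survey data allow: directly if, for example, 2012 and 2015 records can be linked, and otherwise through age-specific caries levels.
3. Replace the two-sample t-test with a regression, or with a per-child analysis of observed minus expected increment. Either should carry the uncertainty of the modelled expectation into the confidence interval.

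**Cost:** participants' age, sex and baseline caries are already collected, so no new measurement is needed on them. The work is extra modelling and a check on whether survey records can be linked. Conditioning on baseline caries may remain only approximate on the expected side, and the report should say so.

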### Analysis

All baseline socio-demographic characteristics will be described for the selected sample using counts and frequencies. Baseline and follow-up caries experience and questionnaire related information will be reported. Dental caries increment (incidence) will be the main outcome measure used to determine the effectiveness of the preventive intervention. The expected caries increment will be modelled from the three oral health surveys conducted in this community (2004; 2012 and 2015) and compared with the actual caries increment from 2015–2016; 2016–2017 and 2015–2017. The mean caries increment will be compared between the expected (modelled) and actual findings, and adjusted for known risk factors for dental caries. The hypothesis will be that caries increment observed in the period of 2015 to 2017 is smaller than the modelled caries increments. Two independent samples *t*-test will be used for the analysis with significance being determined if *p* < 0.05.

Children who receive only a part of the intervention will be separately assessed: for example we will have children who fully participate, those with baseline and only a year 1 follow-up, those with baseline and only a year 2 follow-up. This will ‘naturally’ further inform us on the most appropriate frequency of this preventive strategy. Both a group and matched analysis will be conducted to account for children who receive only part of the intervention.

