One of the reasons for the improved oral health status could be due to fluoridation of the local water supplies. Whilst the economic viability of water fluoridation for a small community such as this might be questioned, we posit the costs are outweighed by the significant caries reduction in both the deciduous and permanent dentitions as found in our study [18]. Moreover, the fluoridation plant has functioned erratically since being implemented and has been out of operation since April 2011 following a lightning strike. The likelihood that the water will again be fluoridated is uncertain due to budget constraints and because the 2012–2015 Queensland State Government legislated to give local governments across the State the power to decide to fluoridate or not. Dental caries rates may again increase in the absence of water fluoridation. It will be crucial to investigate alternative models to ensure improvements in dental caries incidence in this resource-constrained community. The envisaged dental prevention model will essentially reduce the microbial load with the topical disinfectant, povidone iodine [10]; inhibit biofilm adherence to susceptible sites by application of fissure sealants [19] and reduce the susceptibility of the tooth to demineralisation by acids generated in the microbial biofilm by the application of a fluoride varnish [9, 20]. Measures of local fluoride concentration [20] and of oral mutans streptococci counts return to baseline after a few months [21], so that most reported studies have used regular re-applications (2–4 times per annum), which would be difficult to implement in remote settings lacking appropriately trained personnel and resources. Fissure sealants, on the other hand, have excellent longevity [19].

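### The expected caries increment is modelled from surveys with different fluoridation histories, but the stated adjustment set omits age, baseline caries and fluoride exposure or survey period

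*Protocol article*

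**What the plan says.** Under Study design, the article says that no control group will be created. Children who do not consent may serve as natural controls if they agree to an examination at the end. The planned comparison is therefore between the observed increment and an expected one. Under Analysis: "The expected caries increment will be modelled from the three oral health surveys conducted in this community (2004; 2012 and 2015"). Study design gives the fluoridation status of the surveys: "in 2004 (pre-water fluoridation); in 2012 (by the Griffith University team post-partial water fluoridation) and 2015 (baseline survey for this study").

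The Background section on the burden of caries describes what happened between them. "Age-weighted overall caries prevalence and severity declined from 2004 to 2012 by 37.3" per cent, with the largest change in younger children. Fluoridation is offered as one possible reason. The plant, however, "has been out of operation since April 2011 following a lightning strike", and the authors add: "Dental caries rates may again increase in the absence of water fluoridation".

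The Covariates section says that the relationship between outcomes and intervention "will be adjusted for known risk factors for dental caries - oral hygiene behaviours and diet (sugar consumption"). The Analysis section refers again to known risk factors without naming more, and names a two independent samples t-test. Under Study design, the questionnaire covers age and "residential history (exposure to fluoridated drinking water"). Under Primary outcome variable, caries is scored at baseline by ICDAS-II.

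**The concern.** The expected increment stands in for the children's course without the programme. It should describe untreated children of the same ages, with the same starting disease, in 2015 to 2017. The source surveys describe children with different fluoride exposure. The November 2012 survey was itself taken about 1.6 years after the plant stopped.

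The article treats the unlisted variables as important. The 2004 to 2012 fall varied with age, participants are 4 to 17 years old, and the opening of the Background calls deciduous caries a predictor of permanent caries. Leaving these out of the stated adjustment lets a calendar change in caries be read as an effect of the intervention, or cancel one.

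The consequence goes beyond the primary test. Under Transition probabilities, the non-intervention rates in the Markov model come from the same modelled data, so an error passes into the cost-effectiveness results.

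**Working it through.** The article states no sample size, power or expected increment, so there is no planned figure to reproduce. The check shows how far the expected value can move with the part that 2004 plays in it.

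**Inputs from the article (Burden of dental caries section)**
- Overall age-weighted decline, 2004 to 2012: 37.3%. With 2004 set to 1, the 2012 level is 1 − 0.373 = 0.627.
- Mean decayed score at age six: 5.20 in 2004 and 3.43 in 2012. The fall is (5.20 − 3.43)/5.20 = 34.0%.

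**Assumptions, none of them in the article**
- The increment is proportional to the survey level.
- The 2015 survey level equals that of 2012.
- The expected value is a weighted mean with weight w on 2004: E = w × (2004 level) + (1 − w) × (2012 level). Equal weighting of three surveys means w = 1/3.

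**Case A: the untreated level in 2015 to 2017 is still the 2012 level, and the intervention does nothing.** The apparent reduction is (E − 0.627)/E.

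| w | E | Apparent reduction |
|---|---|---|
| 1/4 | 0.720 | 12.9% |
| 1/3 | 0.751 | 16.5% |
| 1/2 | 0.814 | 22.9% |

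At w = 1/3 the expected value is too high by 0.751/0.627 − 1 = 19.8%. The age-six scores give E = (5.20 + 3.43 + 3.43)/3 = 4.02 and an apparent reduction of (4.02 − 3.43)/4.02 = 14.7%.

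**Case B: the untreated level has gone back to that of 2004.** At w = 1/3, an intervention with no effect looks 1/0.751 − 1 = 33% worse than expected. A true reduction of 1 − 0.751 = 25% would show as no difference. Dropping 2004 altogether gives E = 0.627, which is 37.3% below the untreated level, so leaving 2004 out is not automatically safer.

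**Effect on the test in case A.** The chance of a significant result with no true effect was computed for a two-sided test at 0.05. The group size was assumed to be 200 to 400, and the SD 1 to 2 times the mean increment.
- w = 1/3: 17% (n = 200, SD twice the mean) to 80% (n = 400, SD equal to the mean).
- w from 1/4 to 1/2: 11% to 99%.

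The range is too wide to quote a single rate. In every scenario of case A it exceeds the nominal 5%.

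**The case against.** The article says that the increment is modelled from the surveys. It does not say that they are pooled or how they are weighted. A cross-sectional survey yields an increment only through differences between ages or between surveys, so age or period probably enters the model somewhere. An article may leave the form of a model to the full protocol or SAP. The Covariates section concerns the relationship between intervention and outcome, which is a different step from building the expected value. The 2015 baseline survey is one of the model's inputs, and the outcome is a change from that baseline, so baseline caries is not ignored altogether. The 37.3% refers to prevalence and severity, not to increment, and fluoridation is only one possible reason for it.

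All of this stands, and it limits the point. It does not remove it: the article does fix an adjustment set, names two variables in it, and pairs it with a t-test that cannot carry covariates.

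A reader might go further in four ways that the article does not support:
- That the plan averages the surveys equally, or has a particular false-positive rate. No weights, SD or analysed numbers are given, and the result depends almost wholly on what is assumed.
- That adjusting for each child's fluoride history would separate the fluoridation trend from the intervention. That history is shown to be collected only for study children, not in 2004 or 2012. Covariates known only in treated children cannot remove a calendar trend.
- That children examined in both 2012 and 2015 should supply the main comparator. Nothing says that the records can be linked or how many children remain. The interval is about three years, and the youngest children would be missing.
- That effectiveness should be claimed only if the results with and without 2004 agree. In case B the analysis without 2004 is the more biased one, so such a rule could suppress a real benefit.

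**Conclusion.** The concern holds in limited form. The planned comparator draws on surveys that the article itself separates by fluoridation status, and the stated adjustment set leaves out age, baseline caries and fluoride exposure or period. The article's own figures make the possible shift material. Under equal weighting and an unchanged untreated level, the expected value is about 20% too high and a 17% reduction appears from nothing. Under a return to the 2004 level, a benefit of about 25% could vanish. Both figures rest on proportionality between survey level and increment, on equal weights, and on a 2015 survey level equal to that of 2012. The actual size and direction are unknown until the model is stated.

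This is an inexpensive improvement to the only planned comparator. It does not show that the planned analysis must give a false result.

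**What to change.** In the Covariates and Analysis sections:

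1. State that the expected-increment model includes age, baseline (2015) caries, and survey period or fluoridation status. Say which period's level is projected forward to 2015 to 2017.
2. Carry the same terms into the comparison of observed and expected increments, by a regression in place of the unadjusted t-test. All treated increments fall in 2015 to 2017, so period acts there only through the expected value.
3. Use individual years on fluoridated supply only where the earlier surveys recorded them. Otherwise let survey period or fluoridation status stand in.
4. Report the primary contrast with and without the 2004 survey as a sensitivity analysis, and discuss any difference in the light of the stopped plant.
5. If the 2012 and 2015 records can be linked, report the increments observed before the intervention as supportive evidence only.

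The cost is a change of wording and a little more analysis, using variables already collected in study children. The conclusion may be less firm if the results with and without 2004 differ.

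### The expected increment rests on surveys taken under changing water fluoridation, yet the stated adjustment set omits the fluoride exposure the study collects, so a background change can mimic or hide an intervention effect

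*Protocol article*

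**What the plan says.** All places are in the protocol article.

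- **Comparator.** Study design states that no control group will be formed. Analysis sets the reference value: "The expected caries increment will be modelled from the three oral health surveys conducted in this community (2004; 2012 and 2015". The actual increments for 2015–2016, 2016–2017 and 2015–2017 are compared with it.
- **Fluoridation at each survey.** Study design labels two of the three surveys: "in 2004 (pre-water fluoridation); in 2012 (by the Griffith University team post-partial water fluoridation". The 2015 survey carries no such label.
- **What happened to caries and to the plant.** The Background section on burden reports: "Age-weighted overall caries prevalence and severity declined from 2004 to 2012", by 37.3%, and at age six a mean decayed score falling from 5.20 to 3.43. It offers fluoridation as one possible reason. It says the plant ran erratically and "has been out of operation since April 2011 following a lightning strike", calls a restart uncertain, and warns: "Dental caries rates may again increase in the absence of water fluoridation".
- **Adjustment.** Under Covariates, outcomes are to be "adjusted for known risk factors for dental caries - oral hygiene behaviours and diet (sugar consumption".
- **Data collected.** The questionnaire in Study design includes "residential history (exposure to fluoridated drinking water".
- **Economic model.** Transition probabilities takes the non-intervention rates from the same modelled data.

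**The concern.** With a historical comparator, any background driver of caries that differs between the reference surveys and the trial years falls directly into the effect estimate. The protocol identifies such a driver itself, reports a large shift in caries over the period in which it changed, and collects a measure of each child's exposure to it. It then states an adjustment set without it.

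At stake is the main hypothesis, that the actual increment is lower than the expected one. If the expected value sits above what untreated children would now experience, an ineffective programme looks effective. If it sits below, a working programme looks weak or harmful. More children would not help, because this is bias and not imprecision. The incremental cost-effectiveness ratio inherits the error through the non-intervention transition probabilities.

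**Working it through.** **The protocol's own figure.** The 37.3% fall cannot be reproduced, because the age-specific means and weights are not given. The age-six scores allow a check of direction and rough size: (5.20 − 3.43) / 5.20 = 34.0%.

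**Inputs.** From the article: the 37.3% fall, and 5.20 and 3.43 at age six. Assumed: increment is proportional to caries level; the intervention has no effect; the true level in the trial years equals the 2015 level. The 2015 level is not given, so it is varied. Set 2004 = 100; then 2012 = 100 × (1 − 0.373) = 62.7.

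**Formula.** Spurious effect = actual / expected − 1. A negative value is a false reduction, a positive value a false excess.

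**Case 1: 2015 equals 2012, equal averaging of the three surveys.**
- Age-weighted: expected = (100 + 62.7 + 62.7) / 3 = 75.1; 62.7 / 75.1 − 1 = −16.5%.
- Age six: expected = (5.20 + 3.43 + 3.43) / 3 = 4.02; 3.43 / 4.02 − 1 = −14.7%.

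**Case 2: 2015 equals 2012, least-squares line projected to 2016.** The mean year is 2010.33 and the slope −3.653 per year. Expected = 75.13 − 3.653 × 5.667 = 54.4; 62.7 / 54.4 − 1 = +15.2%.

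The same data and the same null effect thus give opposite signs under two simple ways of combining the surveys.

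**Case 3: caries has rebounded by 2015.** The same formulas, with the 2015 level raised above 62.7:

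| Rebound over 2012 | 2015 level | Mean of three surveys | Spurious effect | Mean of 2012 and 2015 only | Spurious effect |
|---|---|---|---|---|---|
| 0% | 62.7 | 75.1 | −16.5% | 62.7 | 0% |
| 10% | 69.0 | 77.2 | −10.7% | 65.8 | +4.8% |
| 20% | 75.2 | 79.3 | −5.1% | 69.0 | +9.1% |
| 30% | 81.5 | 81.4 | +0.1% | 72.1 | +13.0% |
| Full return to 2004 | 100 | 87.6 | +14.2% | 81.35 | +22.9% |

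Under averaging, the bias runs from a false reduction of about 17%, through roughly zero at a 30% rebound, to a false excess of about 14%. The last two columns show that leaving out 2004 does not remove the problem: once caries has rebounded by 20% or more, it makes the bias larger.

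**Do other planned elements cure this?** The possible natural controls in Study design are children who decline to take part and are examined only at the end. They are self-selected, and without a baseline examination no increment can be computed for them. The univariate and probabilistic analyses under Cost utility analysis vary parameters around their estimates; they do not address a reference value that is itself displaced.

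**The case against.** The strongest reply is that the article does not specify the expected-increment model. The Covariates section governs the adjustment of outcomes, and a fuller plan could carry fluoridation in the model itself. The authors clearly know of the issue, since they label two surveys by it and collect exposure. This stands in part. A reader might infer that fluoride is absent from the counterfactual model, but the article does not say so. What it does state is the set of three surveys and an explicit adjustment list that omits a collected variable. A fuller plan would at least have to extend that list.

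The sizes above also belong to models chosen for illustration. The protocol proposes neither equal averaging nor a straight line, and proportionality of increment to caries level is an assumption. That stands, and it is why no single figure is claimed.

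Four stronger readings are tempting and not supported:

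- *The design will make an ineffective programme look effective.* The sign is indeterminate, as the table shows.
- *The whole 37.3% is due to fluoride.* The article says only that fluoridation could be one reason, although any other secular change would bias a historical comparator in the same way.
- *The surveys fall under three documented fluoridation conditions.* Only 2004 and 2012 are labelled. The 2015 condition is inferred: about four years without fluoridation if the plant stayed off. The November 2012 survey itself came about 19 months after the shutdown.
- *The 2004 survey should be dropped from the primary model.* It is the only pre-fluoridation survey, and dropping it can enlarge the bias.

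**Conclusion.** The concern holds. The only comparator for the primary effectiveness test is modelled from surveys that the protocol itself ties to changing fluoridation, and the stated adjustment omits fluoride exposure although it is collected. A background change in fluoridation can be read as an intervention effect or can hide one, and the error carries into the non-intervention side of the economic model.

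Direction and size are not determined by the article. Under the stated assumptions the illustrations run from a spurious reduction of 15–17% to a spurious excess of 14–15%, with almost none at a 30% rebound under averaging. They show that the result is sensitive to an unstated choice; they do not forecast the bias. Confidence is high that the vulnerability exists and low on its magnitude.

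**What to change.** 1. Add exposure to fluoridated water to the Covariates list and to the expected-increment model. Use residential history where it was collected; for the earlier surveys, use birth date set against the plant's operating dates.
2. Freeze the model and its predicted increments after the 2015 survey and before the first follow-up examination.
3. Keep 2004 as the pre-fluoridation reference. Report how the primary result and the incremental cost-effectiveness ratio change with and without each survey, and under alternative assumptions about fluoridation in 2015–2017.
4. Record any plant restart in 2015–2017 and treat it as a sensitivity scenario. All participants are offered the intervention, so trial data alone cannot separate a restart from calendar time.

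The cost is revised wording and modest extra modelling, with no new arm. The limitation is that individual exposure may be only approximate for the 2012 survey, since the article does not say that it was recorded then, and the plant's erratic running blurs any reconstruction from dates.
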